#### Gait Speed

The participant will be asked to walk down a hallway through a 1-m zone for acceleration, a central 5.5-m testing zone, and a 1-m zone for deceleration. The participant will be asked to walk down the testing zone at normal gait speed and as fast as possible without running, and not to slow down before the 5.5-m mark. Normal gait speed and maximal gait speed will be recorded once.

#### 30-Second Sit-to-Stand Test

We will measure lower extremity strength and endurance with the 30-second sit-to-stand test. The participant will be asked to sit in a standardized chair (a 43-cm high chair, without arm rests, placed against the wall) and asked to sit in the middle, back straight, feet approximately hip width apart and placed flat on the floor, with knees 90° flexed. If needed, one foot can be placed slightly in front of the other to help maintain balance. The participant will be asked to stand and sit as many times as possible in 30 seconds keeping their arms crossed against the chest and instructed to fully sit down between each stand. We will record the number of correct sit-to-stands performed in 30 seconds.

#### Quadriceps Strength

We will measure isokinetic and isometric strength of the quadriceps muscle in both legs using an isokinetic dynamometer (Biodex Corporation). Participants will be seated on the dynamometer with a hip angle of 90° flexion stabilized with thigh and pelvic straps. The chair will be positioned so that the medial condyle of the knee is centered with the axis of the dynamometer with little or no gap behind the knee and the edge of the seat. The lower leg will be secured and the calf pad will be placed 5 cm proximal to the lateral malleolus. The range of motion will be set so as to obtain maximal speed during the isokinetic tests (from 90°of knee flexion to –5° of full knee extension) and at 60° for the isometric tests. Prior to each test, the participants will be given the opportunity to become familiar with the procedures and to warm up, by doing 10 submaximal contractions and 2 maximal contractions. For the test, 6 maximal concentric reciprocal contractions and 3 maximal muscle contractions held for 5 seconds will be completed with a 3-minute rest between.

#### Questionnaires

We will obtain demographic information (age, sex, education, ethnicity, employment, income) at baseline using the relevant New Zealand census questions. To measure generic health outcomes from the participant’s perspective, we will use the 12-item Short-Form Health Survey (SF-12) [32]. To measure exercise self-efficacy, we will use the 18-item Exercise Self-Efficacy Scale (ESES) [33]. We will use the 18-item Physical Activity Enjoyment Scale (PACES) to measure perceived enjoyment of physical activity [34]. To assess lifestyle from a multifactorial perspective, we will use the Lifestyle Appraisal Questionnaire (LAQ) [35]. After the 20-week intervention period, we will measure satisfaction and obtain feedback information from the participants by asking the participants, anonymously, to fill out an evaluation questionnaire.

### Termination Criteria

In the event of chest discomfort, failure of HR to increase normally with increased workload, light-headedness, severe fatigue, and shortness of breath, which are all abnormal responses to exercise, we will advise the participant to discontinue that exercise session. If symptoms continue for longer than 24 hours, the participant will be referred to their general practitioner. If symptoms are recurrent or take longer than 24 hours to resolve, the participant will be withdrawn from the study.

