**Methods:**

We will conduct a 40-week, single-blinded randomized controlled trial in 84 middle-aged adults with low appendicular lean soft tissue mass in the wider Dunedin area, New Zealand. We will randomly allocate participants to receive either a group-based, 20-week high-intensity interval aerobic resistance training intervention program or a single, 60-minute education session on current exercise recommendations. After the first 20 weeks, both groups will be given a 20-week home program. The study will assess primary and secondary outcome measures, including body composition (regional and whole-body lean soft tissue mass, fat mass, percentage body fat, measured by dual x-ray absorptiometry), blood biomarkers (cortisol, creatinine, C-reactive protein, lipid profile, hemoglobin), physical fitness (maximum oxygen consumption, blood pressure), physical activity (accelerometry), physical function (handgrip strength, sit-to-stand, gait speed, quadriceps strength), and self-reported questionnaires (health outcomes, self-efficacy, perceived enjoyment of physical activity, and multifactorial lifestyle), at baseline, 20 weeks, and 40 weeks. Physical function and self-reported questionnaires will also be measured at 10 weeks. We will assess the primary outcome measure, total body lean soft tissue mass, at baseline, 20 weeks, and 40 weeks. Analyses will be performed using intention-to-treat principles, comparing the outcomes resulting from the intervention, using linear mixed models.

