### Intervention

#### Control Group

The control group will receive education on current exercise recommendations during a 60-minute group session, provided by a physiotherapist. We will define current exercise recommendations as proposed by the World Health Organization: adults aged 18 to 64 years should do at least 150 minutes of moderate-intensity aerobic physical activity throughout the week, or at least 75 minutes of vigorous-intensity aerobic physical activity, or an equivalent combination of moderate- and vigorous-intensity activity [24]. Following the 20-week intervention, the control group will be offered 3 weeks of supervised exercise, where they are taught how to perform HIART. After 3 weeks, they will be given access to the remainder of the 20-week home program. We will design the home program specifically for this study and it will be viewable with protected YouTube links.

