### Statistical Analysis

All analysis will be conducted in Stata version 15 (StataCorp LP) using the principles of intention-to-treat analysis. We will use descriptive statistics to characterize the groups at baseline. The intention-to-treat analysis for this study will include all participants, including those who are not fully compliant and those with missing outcome data. The primary outcome will be the change in total body lean soft tissue mass. Secondary outcomes include changes in physical fitness, muscle strength, physical function, and blood biomarkers. The primary analysis will compare the primary and secondary outcomes resulting from the intervention, using linear mixed models to model outcomes at T1, T2, and T3 adjusted for baseline values. Standard mixed-model diagnostics will be performed. Group differences will be presented in the form of mean differences for continuous outcomes and an odds ratio for binary outcomes, with their associated 95% confidence intervals.

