## Results

We obtained ethical approval for this study from The University of Otago Human Ethics Committee on December 10, 2018. The project is supported by a University of Otago Research Grant and a Dunedin School of Medicine Dean’s Bequest Fund (January 2019 to March 2020). Patient recruitment started on February 11, 2019 and was completed on May 14, 2019. Data collection started on February 25, 2019 and was completed on February 28, 2020. We enrolled 82 participants. Data analysis is underway and we expect to publish results in January 2021.

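### The symptom rule takes participants out of the study, not just out of training, so 20-week lean mass is lost avoidably and mainly in the HIART arm

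*Protocol article*

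**What the plan says.** The Termination Criteria section lists symptoms such as chest discomfort and breathlessness, "which are all abnormal responses to exercise, we will advise the participant to discontinue that exercise session". Symptoms lasting more than 24 hours lead to referral to a general practitioner. The last step is: "If symptoms are recurrent or take longer than 24 hours to resolve, the participant will be withdrawn from the study". Either recurrence or duration is enough to trigger it.

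Four other places determine what this does to the primary comparison:

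- **Timing of the primary outcome** (Abstract, Methods): "We will assess the primary outcome measure, total body lean soft tissue mass, at baseline, 20 weeks, and 40 weeks". There is no 10-week lean-mass value.
- **What controls do up to week 20** (Control Group): "The control group will receive education on current exercise recommendations during a 60-minute group session, provided by a physiotherapist". Supervised training comes later: "Following the 20-week intervention, the control group will be offered 3 weeks of supervised exercise, where they are taught how to perform HIART".
- **The model** (Statistical Analysis): "using linear mixed models to model outcomes at T1, T2, and T3 adjusted for baseline values".
- **The analysis set** (Statistical Analysis): "The intention-to-treat analysis for this study will include all participants, including those who are not fully compliant and those with missing outcome data".

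The Results section gives the present state of the trial: "We enrolled 82 participants. Data analysis is underway and we expect to publish results in January 2021".

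**The concern.** The section distinguishes ending a session from leaving the study, and for recurrent or persistent symptoms it chooses leaving the study. Nothing elsewhere in the article keeps such a participant in outcome assessment. Stopping the exercise protects the participant. Cancelling a later DXA scan adds no protection and removes the primary outcome.

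An intention-to-treat comparison needs the 20-week outcome of people who stopped training as much as that of people who finished. The rule removes exactly those people, and before week 20 it can act on few outside the HIART arm. Missing 20-week lean mass would then depend on arm and on tolerance of training. If those withdrawn would have gained less than completers, the estimated effect of assignment to HIART is too large.

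The Statistical Analysis section does say that participants with missing outcome data are included, so the two sections do not contradict each other in words. The difficulty is practical: the rule creates gaps that a visit could have filled, and the analysis must fill them by assumption.

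**Working it through.** **Step 1. Who is affected, and when.** The rule is triggered by responses in exercise sessions. In weeks 0 to 20 the trial's sessions are held for HIART only; controls have one education session. A control could develop symptoms in self-directed exercise, so the rule acts mainly, not solely, on HIART. After week 20 both arms are offered HIART and the rule can reach both. The imbalance is therefore a matter for the 20-week comparison.

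**Step 2. What the model receives.** The outcomes are T1, T2 and T3, with baseline as an adjustment. Lean mass has no T1 value. Someone withdrawn before week 20 has neither T2 nor T3, and so contributes no lean-mass outcome. In effect the model treats that person as a HIART completer with the same baseline.

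**Step 3. The plan's own figures.** The plan states no symptom-withdrawal rate. The nearest figure is the 15% allowance for dropout or unusable data (Sample Size). It reproduces: 35 / 0.85 = 41.2, rounded up to 42 per group. It is not split by arm or cause. (The stated 95% power with 35 per group does not reproduce: 1.5 kg, SD 1.9 kg and two-sided 5% give about 0.90 by the t test. Nothing below depends on that.)

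**Step 4. Inputs.**

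- From the article: 82 enrolled and 1:1 allocation, so about 41 per arm; SD 1.9 kg; target difference 1.5 kg.
- Assumed: k = 2, 4 or 6 HIART participants withdrawn before week 20; shortfall g = 0.5 to 1.5 kg in their gain; completers differ from control by 1.5 kg; the withdrawn have baselines like those of completers.

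**Step 5. Formula.** Let completers gain m and the withdrawn gain m − g. With q = k/41:

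- mean gain over all HIART participants = (1 − q)m + q(m − g) = m − qg
- mean gain estimated without the withdrawn = m
- overstatement = q × g

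The standard error of the observed difference is 1.9 × √(1/(41 − k) + 1/41).

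| k | q | Overstatement, g = 0.5 kg | Overstatement, g = 1.5 kg | As % of 1.5 kg | SE (kg) | Overstatement / SE |
|---|---|---|---|---|---|---|
| 2 | 0.049 | 0.024 kg | 0.073 kg | 2–5% | 0.425 | 0.06–0.17 |
| 4 | 0.098 | 0.049 kg | 0.146 kg | 3–10% | 0.431 | 0.11–0.34 |
| 6 | 0.146 | 0.073 kg | 0.220 kg | 5–15% | 0.437 | 0.17–0.50 |

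**Step 6. Check.** Simulating 20,000 trials per case, with week-20 lean mass regressed on arm and baseline and the withdrawn dropped, gave overstatements of 0.025 kg (k = 2, g = 0.5), 0.098 kg (k = 4, g = 1.0) and 0.221 kg (k = 6, g = 1.5). This confirms the algebra; it is no evidence on k or g.

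**Step 7. Power.** With no other dropout, two-sided t-test power is 0.942 for 41 against 41. With 2, 4 or 6 HIART participants lost it is 0.936, 0.930 or 0.923. The loss of precision is minor; bias is the issue.

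**The case against.** The strongest reply is that this is a short safety rule in a condensed article, and that a fuller protocol may say whether scans continue after withdrawal. The size is also assumed throughout. Several features should keep the rate low. Recruits are otherwise healthy adults aged 40 to 50, people with cardiovascular disease or its symptoms are excluded, and high-risk people are screened out. The rest have a 12-lead ECG during a maximal test, with cardiologist approval before entry. Six of 41 would use almost the whole 15% allowance (15% of 41 is 6.15) on this one cause. Some people with persistent symptoms would decline further visits under any wording. The direction is not established either, since someone withdrawn late may already have gained lean mass. And the rule can no longer be changed.

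Much of this stands as a limit on size. Because some would have left anyway, q × g is an upper figure for what the rule itself causes, and screening makes the lower rows of the table more likely. Screening does not rule out recurrent fatigue or breathlessness, however, in sedentary people doing maximal-effort intervals.

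The point about condensation does not remove the concern. The article is not silent: it states a rule, and that rule followed as written ends study participation. The intention-to-treat sentence governs analysis and does not say that withdrawn participants are measured.

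**Conclusion.** The concern holds. Applied as written, the symptom rule produces avoidable missing primary outcomes, mainly in the HIART arm up to week 20 and among people who have stopped training. That undercuts the stated intention-to-treat aim without contradicting it in words.

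The likely size is small to moderate: an overstatement of about 0.02 to 0.22 kg in the 20-week difference. This rests on an assumed 2 to 6 withdrawals among about 41, an assumed shortfall of 0.5 to 1.5 kg, and none of those withdrawn having been measured afterwards. If nobody was withdrawn under the rule before week 20, there is no effect on the 20-week comparison. A bias that inflates the effect is the more plausible direction but is not certain. The point should be addressed, but it does not by itself put the trial's conclusion in doubt.

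**What to change.** **The rule as it should have read.** The participant is withdrawn from exercise training; scheduled outcome assessments continue unless consent is withdrawn. At a minimum these are DXA, bloods and questionnaires, with exertional tests only after clinical clearance. The cost would have been a few non-exertional visits, with no loss of safety.

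**What can still be done while analysis is underway:**

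1. Report symptom withdrawals by arm and by timing (before or after week 20), and state whether any outcomes were collected after withdrawal. This is one line in the participant flow. If there were none before week 20, that line settles the matter for the 20-week result.
2. If there were any, add one sensitivity analysis of 20-week lean mass in which HIART participants withdrawn for symptoms are given control-like changes from baseline, and present it beside the primary estimate.

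Neither step needs new data.

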### Adherence

Strategies to improve adherence will include group-based participation [36], individualized exercise goals, flexibility in rescheduling to another session online, and the use of reminders. We will monitor participation adherence using attendance checklists. Adherence to the set HR goals will be monitored by recording the participants’ HR throughout the exercise sessions using HR monitors (Polar RC3; Polar Electro Oy). Adherence to the home program will be monitored with a self-reported physical activity diary.

### Sample Size

Based on a standard deviation of 1.9 kg and an effect size *f* of 0.39 (obtained from previous literature [37]), our study has 95% power using a 2-sided 5% level of significance to detect clinically meaningful differences in lean soft tissue mass of 1.5 kg between the intervention and the control group with 35 participants per group. We will aim to recruit 84 participants (42 per group), which allows for 15% dropout or unusable data.

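### The stated 95% power does not follow from the sample-size inputs: 35 per group at a two-sided 5% level gives about 90% in a two-group comparison

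*Protocol article*

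**What the plan says.** The power statement is one sentence in the Sample Size section of the protocol article. It opens "Based on a standard deviation of 1.9 kg and an effect size *f* of 0.39", both attributed to previous literature. It then claims that "our study has 95% power using a 2-sided 5% level of significance to detect clinically meaningful differences" and names the target as "differences in lean soft tissue mass of 1.5 kg between the intervention and the control group with 35 participants per group". The next sentence adds the allowance for losses: "We will aim to recruit 84 participants (42 per group), which allows for 15% dropout or unusable data". The section gives no correlation with baseline, no number of repeated measurements and no correlation between them.

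The Statistical Analysis section plans linear mixed models adjusted for baseline and defines the primary outcome as the change in total body lean soft tissue mass. It does not tie that model to the sample size. The Results section reports "We enrolled 82 participants", with data collection complete and analysis under way.

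**The concern.** The sentence supplies everything that a two-group power calculation needs: difference, standard deviation, level, sidedness and group size. It also supplies the result, so the result can be checked, and it does not come out. This is not a matter of detail left to a fuller document, because a complete set of inputs is printed beside a figure that they do not produce.

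At stake is the stated risk of missing a real 1.5 kg effect. A reader would take it to be 1 in 20, whereas the printed inputs put it at about 1 in 10. This matters mainly if the trial finds no clear difference and the planned power is cited to support a negative conclusion.

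**Working it through.** **Inputs** (all from Sample Size; 1:1 allocation from the section on blinding and randomization): difference 1.5 kg, SD 1.9 kg, f = 0.39, two-sided 5%, 35 per group, 42 per group after 15% loss.

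**Step 1. Do the inputs agree?** d = 1.5/1.9 = 0.789. For two equal groups f = d/2 = 0.395, stated as 0.39. Conversely, d = 2 × 0.39 = 0.78. They agree up to rounding, so the stated f is simply the difference over the SD, halved. No variance reduction is built into it.

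**Step 2. Try to reproduce 95%.** Two-sample t test, noncentrality = d × √(n/2), df = 2n − 2 = 68, two-sided critical value 1.995.

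- d = 0.789: noncentrality 0.789 × √17.5 = 3.30; power **90.2%**.
- d = 0.78: noncentrality 0.78 × √17.5 = 3.26; power **89.6%**. The ANOVA F test with f = 0.39 and N = 70 gives the same value.
- Normal approximation: 91.0% and 90.4%.

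No choice of rounding or approximation brings the two-sided figure to 95%.

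**Step 3. What would give 95% at 35 per group?**

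| Reading | Power at 35 per group |
|---|---|
| One-sided 5%, exact t | 94.8% (d = 0.789), 94.4% (d = 0.78) |
| Two-sided, baseline-adjusted, *assumed* correlation 0.4 / 0.5, if 1.9 kg is an unadjusted SD (d = 0.789) | 94.4% / 96.4% |
| Two-sided, repeated-measures between-groups F, 2 measurements, *assumed* correlation 0.6 | 95.4% (f = 0.395), 94.9% (f = 0.39) |

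The baseline-adjusted row uses d/√(1 − ρ²) in place of d. Exactly 95% needs ρ of about 0.43 (d = 0.789) or 0.45 (d = 0.78). The repeated-measures row uses noncentrality N f² m/(1 + (m − 1)ρ): 70 × 0.395² × 2/1.6 = 13.6. The one-sided normal formula for 95% power returns n = 35: 2 × (1.645 + 1.645)²/0.789² = 34.7, rounded up.

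**Step 4. Group size and difference for 95%, two-sided.** Exact t needs 43 evaluable per group (d = 0.789) or 44 (d = 0.78). With 15% loss that is 43/0.85 = 50.6 or 44/0.85 = 51.8, so 51 to 52 recruited per group. Held at 35 per group, 95% power needs d = 0.874, that is 0.874 × 1.9 = **1.66 kg**.

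**Step 5. Recruitment figures.** The dropout step is correct: 35/0.85 = 41.2, so 42.

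- 84 participants, no losses: 94.7% or 94.2% exact; 95.1% or 94.7% by normal approximation.
- 82 enrolled, 41 per group, no losses: 94.2% or 93.7% exact.
- 82 enrolled, 15% lost: 82 × 0.85/2 = 34.9, about 35 per group, so about 90%.

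**The case against.** The strongest reply is that the section does not name the test behind the calculation. It quotes Cohen's f, an ANOVA effect size, and the planned analysis is a baseline-adjusted mixed model. Under such a model, ordinary correlations bring 35 per group to about 95% with a two-sided test, as Step 3 shows. The correlation may stand in the full protocol.

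Part of this stands. A reader might infer that the authors ran a one-sided calculation and labelled it two-sided, since that formula returns 35. The article does not establish this, because other routes reach the same figure. Nor does it show that the power of the planned mixed model is 90%. It shows only that the printed inputs give 90%.

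It does not rescue the sentence. No correlation or number of measurements is stated, and the printed f contains no such gain. Since the primary outcome is a change, 1.9 kg may already be an SD of change, in which case less is left to gain from baseline adjustment. Averaging weeks 20 and 40 would be a doubtful source of gain, because controls are offered the same training after week 20; baseline adjustment at week 20 is free of that problem.

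A reader might also infer that the trial is seriously underpowered, or that 84 participants clearly miss 95%. Neither is supported. About 90% is adequate power, and with all 84 evaluable the shortfall is under one percentage point and vanishes in one normal approximation. The article also commits to 95% confidence intervals, which would carry the reading of a null result better than planned power.

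**Conclusion.** The power statement is wrong as written. From its own inputs, a two-sided 5% comparison of two groups of 35 has 89.6% to 90.2% power by the exact calculation, about 5 points below the 95% claimed. The implied type II error is about 10%, twice the figure a reader would take from the text. This rests on a two-group comparison with 1.9 kg as the error SD, which is the reading that the stated f matches. It would change only if a one-sided test or a correlation was used and left out, and then that omitted input is what needs stating. The fault is one of reporting and does not put the design or the enrolment in doubt.

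**What to change.** Correct the sentence in one of three ways:

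1. State that 35 participants per group give about 90% power, at a two-sided 5% level, to detect 1.5 kg with an SD of 1.9 kg.
2. Keep 95% power and give the detectable difference as 1.66 kg.
3. If the calculation used a one-sided test, or a baseline or repeated-measures correlation, name that test and give its value, and say whether 1.9 kg is an SD of change or of level.

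Carry the corrected figure into the results paper. The cost is one sentence and, under the first two options, a slightly less favourable claim. Recruitment is complete, the dropout allowance is right, and neither enrolment nor the analysis needs to change.
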